## Abstract

**Background:**

Older adults with Mild Cognitive Impairment (MCI) are at high risk of progressing to Alzheimer’s disease (AD). Slowing down the effect of dementia by enhancing brain plasticity represents one of the most prominent challenges. Neurofeedback (NF) has shown promising results in improving working memory but has never been evaluated in people with MCI. We aim to examine whether NF training can decrease cognitive disorders, targeting memory, attention functions and brain electrical activity in elderly patients with MCI.

**Methods:**

In this single-blind, randomized controlled trial (RCT) protocol, we will investigate the effects of two NF training protocols on cognitive performances and on brain electrical activity. Sixty MCI patients will be assigned either to an intervention program or to psycho-pedagogical care as a control condition. Participants in the intervention group will attend 30 sessions of sensorimotor/delta-ratio NF training or beta1/theta-ratio NF training. Neuropsychological assessment, questionnaires and electroencephalography (EEG) assessment parameters will be used as dependent variables in three periods: at baseline (T0), immediately after the last NF training session at 4 months (T1) and at 3-month follow-up (T2). The primary outcome will be the change in attention measured with the Trail Making Test B. Secondary outcome will be the changes in cognitive performance and in EEG activities.

**Discussion:**

If the results of our study show improvement in cognitive performances of older adults with MCI, this non-invasive, low-cost technique may deserve better consideration as a therapeutic intervention to delay cognitive decline and dementia. Consequently, research in NF will need to review and develop the rigor of its application in gerontology.

**Trial registration:**

ClinicalTrials.gov, ID: NCT03526692. Registered on 16 May 2018.

**Electronic supplementary material:**

The online version of this article (10.1186/s13063-018-3170-x) contains supplementary material, which is available to authorized users.

## Background

The concept of Mild Cognitive Impairment (MCI) is an intermediate clinical stage between normal cognitive functioning and mild dementia, indicating a deviation from normal aging [1]. Cognitive changes are noticed by the affected person and/or their family but do not jeopardize the activities of daily life. As used today, MCI is a syndrome rallying diverse pathological disorders affecting older adults [2]. Albert et al. [3] suggested a classification of MCI patients which includes MCI core-clinical, MCI low-likelihood, MCI intermediate-likelihood, and MCI high-likelihood groups, founded on the positivity of amyloid and neuronal injury biomarkers such as cerebrospinal fluid (CSF), beta-amyloid protein 42 (Aβ42) and CSF tau or neuronal injury with the presence of magnetic resonance imaging (MRI)-demonstrable hippocampal atrophy. MCI patients with markers are considered at high risk of developing Alzheimer’s disease (AD) [4]. They provide high motivation for the scientific community to develop pharmacological and non-pharmacological interventions, in order to stop or prevent further cognitive decline and dementia.

### Neuropathophysiology of MCI and AD

Since improvement in algorithms in electroencephalography (EEG) offers a promising approach to developing a database for assessing MCI and AD subjects, several researchers have underscored links between EEG signal and AD/MCI. With age, fast rhythms have been found to decrease [5, 6]. Most commonly in the healthy aging process, EEG changes are not consistently observable but might involve a slight decrease in frequency and amplitude in the alpha band (8–12 Hz), an increase in delta (1–4 Hz) and theta (4–8 Hz) activities unlike young healthy subjects [7, 8]. In AD, theta and delta rhythms are abnormally more dominant in temporal regions of the brain than in other cerebral regions and posterior alpha rhythms significantly decrease [9–13]. Other promising studies in pathophysiology revealed that patients with MCI showed dominant theta activity in the parietal and temporal areas [14–16]. Moretti et al. showed in numerous studies that the abnormal increase in the power ratio alpha3/alpha2 in temporo-parietal brain regions is correlated with hippocampal atrophy in MCI and AD patients [17–19]. Amnestic Mild Cognitive Impairment (A-MCI) subjects present decreased power of the posterior alpha band correlated with cognitive decline [12, 20–22]. Dubois et al. emphasized the decrease in the theta/alpha ratio explained by an increase in alpha oscillations over time in prefrontal areas in people who have Aβ42 deposition and people with prodromal AD. Then, other studies focused on the analysis of the beta band (13–30 Hz) changes at the MCI stage [15]. In recent years, progress in the understanding of MCI and AD pathophysiology has opened several therapeutic perspectives and facilitated the design of more adequate rehabilitation programs [23–27]. Interest in brain-training programs based on sustained cognitive exercises is rising [28, 29]. Non-pharmacological cognitive interventions have been recognized as an efficient method of enhancing cognitive and functional abilities of MCI [30–32].

### Neurofeedback

Neurofeedback (NF), also called electroencephalography Biofeedback (EEG Biofeedback) is one of the promising techniques that received international accreditation boards’ and treatment recommendations of evidence level A from the American Academy of Pediatrics for attention-deficit hyperactivity disorder (ADHD). Other promising results have been found for therapeutic efficacy in autism [33], patients with pharmaco-resistant epilepsy [34], and traumatic brain injury [35]. Neurofeedback uses real-time displays of brain activity—most commonly EEG—to teach self-regulation of brain function. This technique, defined as a closed-loop application, helps individuals to control or modify their cortical activity through learned self-regulation. Precisely, it is operant behavioral training that aims at improving the cognitive functions and that affects regulation by modulating brain electrical activity. The patient receives feedback of acoustic or/and visual signals (graphic or video games/animations/movies) when their rhythmic cortical electrical activity of specific cortical areas has exceeded an upper threshold [36]. The subject has to improve the quality of the signal by a continuing focus in an absolute relaxing state and not exceed a determined upper threshold in a frequency band. The aims are to obtain better alertness and eliminate symptoms of anxiety, consequently inducing better behavior.

Among the protocols of NF training, the sensorimotor brain rhythm (SMR, 12–15 Hz) is an oscillatory rhythm recorded over central scalp regions, generated in a reticular-thalamo-cortical network [37, 38]. SMR/delta NF training involves increasing the synaptic strengths and sensitivity within this network while maintaining low delta activity to avoid sleep (delta, 0.5–4 Hz) [39]. It was suggested that SMR NF training might facilitate thalamic inhibitory mechanisms and block motor activity that interferes with information processing [37]. In accordance with this assumption, few studies found memory and attention improvements after SMR NF training [36, 40–42].

The beta1/theta protocol consists of beta1 dominance (12–16 Hz band) and reduction of theta oscillations (4–7 Hz band) in the central frontal area. Beta1 is described as responsible for logical thinking, concentration, memory and emotional status [43]. Beta2 can be sign of anxiousness; NF training within this range might be conducted with prudence. Theta rhythm is associated with neurological and psychological functions in the limbic system, it serves regulatory control of arousal, affective and mental states [44]. Its excessive presence in frontal areas while the person is awake, indicates a decrease in vigilance with concentration and attention disorders. Thus, an increase in the central frontal beta1 band and a decrease in the central frontal theta band can be linked with an increase in vigilance and concentration and a decrease in diurnal sleepiness [43, 45].

Recently, several studies focused on investigating the benefits of NF training on cognitive functions in elderly subjects. It was shown that elderly patients, who completed a NF training program after stroke to generate SMR modulation on central regions of brain, improved in declarative learning memory [40, 46–50]. Other studies demonstrated increasing performance in working memory in healthy aging with a theta/alpha protocol training on Fz [29, 51] or with an upper alpha training in central regions of the brain [52]. Luijmes et al. [53] observed an increase in learning memory, recognition and recall of information after NF treatment in patients with AD. From a recent pilot study conducted by our research team at the Broca University Hospital in Paris, we investigated the effects of SMR/theta NF training on cognitive performance in elderly patients with MCI. Results showed that cognitive profits were minor, but anxiety decreased and quality of life and sleep improved. EEG data analyzed after the training program indicated that slow frequency bands decreased while alpha and sensorimotor rhythms were more dominant than in pre-training. Furthermore, this study enabled us to identify a few limits in the EEG NF application for older adults with MCI. These preliminary results allowed us to suggest some recommendations to avoid them such as the need to adapt the NF tasks, give explicit information about NF technique and all supplies, and to adjust the threshold to the cognitive and specific profile of the patient.

9pt?>Neurofeedback training seems to be a promising aproach in patients with AD or neurological disorders if this technique is adapted to elderly patients with MCI. On this basis, it would be relevant to further this technique in subjects at risk of developing AD. Based on the studies of Reichert et al. [47], Kober et al. [40] and Luijmes et al. [53], our objective is to examine: (1) the effects of SMR/delta NF training and the beta1/theta-ratio protocols on attention and memory performances in subjects with MCI, (2) to verify whether MCI patients exhibit a decrease or an increase in EEG activities in a resting state after SMR/delta NF training and/or alpha/theta-ratio NF training and (3) to assess the effects of the two training protocols on other cognitive and mood measures.

We hypothesize that (1) central frontal beta1/theta-ratio NF training might be effective in improving attention capacities whereas the SMR/delta protocol in Cz might be effective in improving memory performances and (2) changes in EEG patterns in post-SMR/delta-ratio and beta1/theta-ratio NF training would be observed in the intervention group but not in the control group. This paper has been conceived under consideration of the spirit guidelines (Additional file 1).

## Methods

### Study design

This study is a prospective, randomized controlled and single-blinded clinical trial as shown in Fig. 1. This study will be reported in accordance with both the Consolidated Standards of Reporting Trials (CONSORT) Statement, the CONSORT Statement for non-pharmacological treatment interventions and respecting Neurofeedback Protocol Guidelines [45]. One of the main investigators will inform patients, verbally and in a written document, of the objectives of the study, the project progress with EEG and neuropsychological assessments, and the potential risks. Each participant will be asked to sign a written consent form to ensure their voluntarily participation along with the information that they have right to discontinue the project any time without penalty and their agreement for the use of collected data. Signed consent forms will be kept by the main investigators.

**Fig. 1 Fig1:**
[figure not shown]
Experimental design, representation of the assessment and intervention

### Randomization

After screening and obtaining their written consent, participants who are deemed eligible for the study will be enrolled and the randomization schedule will be designed to yield an assignment ratio of 1:1:1 between the three arms. Randomization will be centralized (CleanWEB; Telemedicine Technologies) and not stratified by blocks of variable size. No one from any group will know if they belong either to an experimental group or the control group (Fig. 1).

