The NF experiment will consist of 30 sessions, twice or three times a week during a maximum of 4 months. From our previous pilot study described above and carried out by our multidisciplinary team (data unpublished), we noticed that the nature of the task in NF training was very important to keep motivation and concentration in our sample. To avoid sleepiness or annoyance, we chose to keep the video of historical reportage as a NF task that had been unanimously appreciated. Thus, during the 30 sessions, videos of historical reportage will be watched for 40 min, divided in eight rounds of 5 min with 20-s break between. Session will last 45 min (Fig. 2). The breaks prevent drowsy episodes and permit the recommencing of sustained attention. The rest of the video will be shown at the next training. The subject receives visual and auditory feedback. To modulate brain activity in the SMR frequency band or in the beta1 band, the video will indicate a bad contrast and a particular sound each time the thresholds are not reached. The degree of difficulty will be manually adjusted by defining the thresholds. As a second feedback, a horizontal bar will be presented on the corner of the patient’s screen showing their real-time SMR power, delta power, beta1 power and theta power according to the threshold. When the expected band power reaches the predefined threshold, the color of the bar will change from red to green. Participants are instructed to try to voluntarily increase this bar to the green color. Neurofeedback training will be conducted by a PhD candidate experienced in neuropsychology, neurophysiology and NF.

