## Discussion

To our knowledge, this study is the first RCT using an SMR/delta-ratio NF group, a beta1/theta-ratio NF group of elderly patients with MCI. Design of our study is not the “gold standard” that would be a placebo-controlled, randomized, double-blind study. Nevertheless, research in NF has to consider the specificity of the application and the protocol to use the technique correctly. Even if different methods are used in different laboratories, the technician trained in NF needs to have control of the protocol and the modulation of the threshold during each training session. Accordingly, in our study, blinding technicians during NF training is not possible. In contrast, psychologists, neurophysiologist assessors, and the statistician analyst are blinded to the participants’ training conditions.

Patients can follow the training with instructions to understand the rules and goals of the activities. They cannot be totally blinded to the treatment condition.

In studies using sham NF training for the control group, the feedback features were signals from other subjects or from a mixture of noise. If we consider that NF training influences behavior, cognitive performance, alertness, mood and brain activity, then training from wrong NF signals might influence one or a few of these parameters in a positive or negative way. In any case, wrong NF signals induce changes, such as frustration of failure, while the subject’s concentration was positive. Incoherence of NF signals with the person’s behavior and alertness is an ethical scientific dimension that needs to be considered for future studies in NF.

We have not defined stopping criteria of the study because we do not expect side effects. EEG NF is a safe and well-established technique. However, the principal investigator will decide if the participants can continue or stop the study if side effects are reported.

The results of this study may be relevant in several aspects. First, there is a need for more research in the field of NF to develop rigorous application while recognizing the necessary adaptation to the conditions of elderly patients with MCI. Then, positive results in our pilot study will allow for the development of a larger population study and for experiments in other diseases, such as AD and epilepsy, in aging. This study will also enable us to obtain complete information regarding the correlation between neurophysiology and cognitive functions in elderly patients with MCI.

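### The Randomization section says no participant will know whether they are in a neurofeedback or the control group, which the Discussion and the described sessions contradict

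*Protocol article*

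**What the plan says.** Three places in the protocol article bear on who is blinded.

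- **Study design** calls this a "prospective, randomized controlled and single-blinded clinical trial" and does not say there which party is blinded.
- **Randomization** then speaks about the participants: "No one from any group will know if they belong either to an experimental group or the control group".
- **Discussion** concedes that the design is not a placebo-controlled double-blind one. It says of patients that "They cannot be totally blinded to the treatment condition" and of the NF staff that "blinding technicians during NF training is not possible". It places the blinding elsewhere: "psychologists, neurophysiologist assessors, and the statistician analyst are blinded".

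The Cognitive outcomes, EEG data acquisition and Methods against bias sections also describe blinding of those who assess outcomes or read the EEG. None of the three claims blinding of participants.

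**The concern.** The Randomization sentence and the Discussion sentence cannot both describe the same trial. The first is Methods text, which a trial report or a risk-of-bias assessment would draw on for the blinding item. Because Study design leaves the blinded party open, the Randomization sentence, which follows shortly after, leads the reader to take single-blind as meaning that the patient is blinded.

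What is at stake is the interpretation of the NF-versus-control contrast. On outcomes that the patient answers, a blinded assessor does not remove what the patient knows. The GDS and the Goldberg Anxiety Scale, both listed as secondary outcomes, are of this kind. The Background reports that in the team's own pilot, which used a related NF protocol, cognitive gains were minor while anxiety fell. So one area where a benefit has already been seen is among the outcomes most open to expectation.

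**Working it through.** No arithmetic applies, and the plan gives no figure to reproduce. The check is whether the Randomization sentence can be true given the procedures described.

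**1. What a patient is told beforehand.** Under Study design, an investigator will "inform patients, verbally and in a written document, of the objectives of the study", together with the course of the project. Under Quality assurance, each participant, whatever the later allocation, meets the NF trainer and is shown the equipment and a demonstration of NF training before the baseline assessment.

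**2. What an NF patient experiences.** Under Neurofeedback training, the video loses contrast and a sound is heard when thresholds are missed. A bar on the screen shows real-time band power and changes from red to green. "Participants are instructed to try to voluntarily increase this bar to the green color".

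**3. What a control patient experiences.** Under Control group condition, the patient watches the same video material, is asked to attend to dates, names and topics, and then answers questions aloud. No feedback is described. There is no sham NF, and the Discussion argues against using it.

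**4. Putting 1 to 3 together.** A control patient has seen NF demonstrated and then attends sessions without it. An NF patient attends sessions that match the demonstration. NF is therefore distinguishable from control by its content.

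**5. Readings that might save the sentence.**
- *Allocation concealment.* The sentence is about members of a group knowing which kind of group they belong to. That is knowledge after assignment.
- *Masking between the two NF protocols.* This may be achievable, but the sentence concerns experimental versus control.
- *Patients not told which arm is the experimental one.* This is hard to sustain when they are informed of the objectives and shown NF in advance.
- *Single-blind meaning assessor-blind.* This fits the rest of the article and is probably what is meant. It does not make a statement about participants true.

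**6. Which outcomes are exposed.** The GDS and Goldberg scales depend on the patient's answers, and at T1 and T2 the patient has already attended the programme. TMT B is a timed test given by a blinded neuropsychologist, so it is less exposed, although performance still depends on effort.

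**The case against.** The strongest reply is that the article already discloses the limit. The Discussion says plainly that blinding is incomplete, explains why sham was rejected and names the blinded roles, and other sections repeat the assessor blinding. Someone who reads the whole article would not credit full participant blinding. This stands as a reason to keep the point small and not to criticise the choice of an active control without sham. It does not repair the Methods sentence: the disclosure confirms that the sentence is wrong.

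The reply is also right on several limits, and a reader might be tempted past them.

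- *That every one of the 60 patients will know their group.* The Discussion says patients cannot be totally blinded, which leaves room for partial masking. All arms see the same video material, the control is an active programme, and the consent pages are not shown. The supportable statement is that blinding to NF versus control cannot be relied on.
- *That the session lengths reveal the allocation.* The NF section says "Session will last 45 min", while the control description mentions 40 min of video and a last 20 min of questions. A patient sees only their own session, so a difference in length shows nothing by itself. Whether the questions come after the 40 min or within it is also not certain. Contact time is a separate matter of matching attention.
- *That the two mood scales are purely self-completed.* The GDS is called a questionnaire and the Goldberg a rating scale, and questionnaires are completed with a blinded neuropsychologist. The exact mode is not stated. What matters is only that the patient supplies the answers.
- *That the pre-baseline demonstration should be moved.* Its stated purpose is to support motivation and retention. Moving it would not remove the contradiction, since the sessions themselves would still differ.

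**Conclusion.** The point holds as an internal inconsistency: the Randomization sentence states a property that the Discussion denies and that the described sessions do not provide. It is wrong as written and should be corrected.

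Its reach is limited. It concerns NF versus control, not one NF protocol against the other. It bears most on the GDS and Goldberg scales and less on the primary outcome. A reader might infer that the primary result is biased in favour of NF. The documents give no basis for the size or net direction of any expectation effect, and the comparator is itself an active programme. The conclusion rests on the sessions being run as described and on each participant receiving the demonstration that Quality assurance promises.

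**What to change.** Replace the sentence under Randomization with, for example:

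> Participants cannot be reliably blinded to NF versus control, and NF trainers are not blinded; cognitive assessors, the EEG reader and the statistical analyst are blinded.

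Under Study design, say that single-blind means assessor-blind. Add a line stating that differences between NF and control, above all on the GDS and Goldberg scales, are to be interpreted as a comparison with an active programme without assured participant blinding.

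The cost is wording only. No procedure, session, sample size or test changes, and the pre-baseline demonstration can stay where it is.
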